#### 4. Summary

**Rationale:** The use of high-dose chemotherapy (HDC) and autologous stem cell transplantation (SCT) has improved the outcome of hematologic malignancies such as multiple myeloma and (non-) Hodgkin's lymphoma. However, the long term side effects of this treatment can have a strong negative impact on quality of life. Patients often complain of severe and persistent fatigue and are compromised in their ability to perform normal physical activities. Physical exercise interventions after SCT can have positive effects on physical fitness, quality of life and fatigue. However, the trials conducted so far were of poor to moderate quality, with methodological shortcomings related to trial design, sample size, choice of comparison groups, outcome measures and duration of follow up. There is a need for a rigorous, appropriately controlled assessment of the effectiveness and cost-effectiveness of exercise in these patients.

**Objective:** (1) To evaluate the effectiveness of an individualized exercise program in comparison to standard care with respect to fatigue, physical fitness and health-related quality of life in patients with hematologic malignancies who have undergone HDC and autologous SCT. (2) To evaluate the cost-effectiveness of this exercise program.

**Study design:** (1) Multicenter, prospective, single blind randomized controlled trial.

**Study population:** Patients ( $\geq 18$  years) with multiple myeloma or (non-)Hodgkin's lymphoma who have undergone induction chemotherapy followed by HDC and autologous SCT.

**Intervention:** The patients (n=120) will be randomized to one of two groups: (1) exercise intervention + standard care (n=60) or (2) standard care (n=60).

**Main study parameters:** At baseline, at completion of the intervention and at 12 months follow-up cardiopulmonary fitness, muscular strength, fatigue and secondary outcome measures will be assessed.

## 5. Background

The use of high-dose chemotherapy (HDC) and autologous stem cell transplantation (SCT) has improved the outcome of hematologic malignancies such as multiple myeloma (MM) and (non-) Hodgkin's lymphoma (NHL/HL). It has become standard of care in these diseases in first line and at relapse respectively. However, the long term side effects of this treatment can have a strong negative impact on quality of life [1]. Up to 75% of patients interviewed at least twelve months post-SCT report severe and persistent fatigue, and are compromised in their ability to engage in normal physical activities [2] About 30% is not able to return to work during the course of the first two years after treatment [3]. Physical deconditioning, resulting from diminished cardiovascular and pulmonary function, reduced muscular strength and cachexia were also highly prevalent [4]. With increasing survival rates, attention should not only be focused on improving cure rates but also on improving recovery after treatment, thereby increasing long-term quality of life. Preliminary results show that exercise interventions can counter the physical deconditioning after SCT, and thus might also improve the quality of life in these patients.

### 5.1 Exercise interventions in the literature

There are a few trials that focused specifically on the effects of physical exercise in patients with hematologic malignancies treated with HDT and SCT. These trials suggested that exercise intervention programs during or after HDT and SCT can improve physical performance, quality of life and fatigue status [see for example 5,6,7,8,9,10,11,12]. Systematic reviews of Liu et al., 2009 and Wiskemann & Huber, 2008 also found encouraging results of exercise intervention studies in these patients. Among these results were an increase in physical fitness, health-related quality of life (HRQL) and psychological well-being. No unexpected or negative effects were encountered. Despite these good results, the systematic reviews conclude that further research is necessary [13,14].

In the study of Liu et al., 2009, only three of the eight reviewed exercise intervention studies were randomized controlled studies. The overall quality of many studies reviewed was limited, with shortcomings related to trial design, sample size, choice of comparison groups, outcome measures and duration of follow up [13]. Wiskemann & Huber support these conclusions [14]. These reviews show that there is a need for well designed, randomized clinical trials using a well defined study population, an appropriate control group and valid and reliable outcome measures to confirm the findings of these trials and to facilitate evidence based therapy.

The trials performed thus far were also very heterogeneous in terms of the type of interventions used, i.e. aerobic exercise versus strength versus mixed-type, moderate versus high intensity exercise, and home-based versus clinically supervised training. Most of them have focused on isolated aerobic exercise during or after the stem cell transplantation. Strength exercise programs and combined intervention strategies have been employed rarely [13,14]. This is somewhat surprising since muscle atrophy is a common problem in cancer patients [15,16]. Normally, muscle atrophy results from a sedentary lifestyle. In cancer patients, muscle atrophy can also be induced by the effects of tumor factors and the side-effects of medication (e.g. glucocorticoids or chemotherapeutic agents [4,17,18]) on skeletal muscle structure and function. These effects are even more pronounced in patients undergoing HDC and SCT, because of the nature of the drugs being used (among others high dose steroids and neurotoxic agents), and because of the morbidity associated with the neutropenic phase after SCT (fever, infections, mucositis, malnutrition) often leading to prolonged bed rest. Considerable evidence suggests that the ability to perform physical tasks in daily life is determined by a threshold level of muscular strength [19]. It is therefore important that exercise interventions aim to minimize muscle atrophy or even stimulate muscle hypertrophy.

Skeletal muscle has shown great adaptability with appropriate training stimuli even in cases of severe muscle atrophy and fatigue [4]. Progressive strength exercise has been shown to increase lean body mass, muscle protein mass and contractile force, and improve physical function in healthy young and elderly subjects [20]. As a consequence, strength exercise in cancer patients seems to be a potent physiological intervention for regaining lost muscle mass and improving muscle quality, ultimately resulting in improved physical fitness, reduced fatigue and an improved overall quality of life [21,22].

Considering the usefulness of both resistance and endurance exercise, an exercise program that combines these two exercise types seems optimal. An example of such a program is the high intensity strength and interval endurance training program developed at the Maxima Medical Center (MMC) in Veldhoven. This study builds on the preliminary results of this exercise program.

## 5.2 Preliminary results

### 5.2.1 Exercise intervention program

In 2008, de Backer et al. developed an 18 week high intensity strength and interval training program for application after chemotherapy. Fifty-seven patients (age 24 to 73 years) who had received chemotherapy for lymphomas, breast, gynaecologic, testicular, or colorectal cancer completed the program [23,24].

Outcome measures were changes in muscular strength, maximal aerobic capacity ( $VO_{2\max}$ ), body composition (using DXA) and HRQL. The high-intensity strength exercise program was well tolerated by all patients. The adherence rate was 84% (6 patients dropped out because of cancer recurrence, and 5 patients because of other reasons such as personal reasons, not interested anymore, disease of the spouse, malaise). Significant improvements (30 to 105%) in muscle strength were found with effect sizes varying from 1.32 to 2.68.  $VO_2\max$  increased significantly by 10% in men and by 13% in women, with an average absolute increase of 3.5 ml/kg/min. Improved levels of  $VO_{2\max}$  may reduce the strain of daily activities, and consequently may allow for more moderate intensity activities such as household activities and walking. Different functional scales of HRQL improved ( $p<0.01$ ), with effect sizes varying from 0.47 to 0.82. Fatigue diminished significantly after exercise by 50% with an effect size of -0.83 ( $p<0.01$ ). Muscle strength correlated significantly with physical functioning before and after the exercise program.

Since this study lacked a control group, 49 patients who followed the high intensity strength training program were compared with a historical control group of 22 patients treated with chemotherapy in the same period but not participating in a rehabilitation program [24]. Compared with the historical control group, muscle strength at one year follow-up was significantly higher in trained patients. Hierarchical multiple regression showed that muscle strength accounted for an additional 24% ( $F=19.07$ ;  $p<0.001$ ) of the variance in physical functioning. Based on these results it was concluded that a supervised, high-intensity strength and interval training program has persistent and substantial beneficial effects on muscle strength, maximal aerobic capacity, and HRQL in cancer survivors after treatment.

Although not included in a formal study, [name] at MMC has in the last few years trained 8 patients who had undergone a stem cell transplantation because of a hematologic malignancy. All 8 patients completed the exercise program and rated it very positively. There were no adverse effects. Compared to the whole group of cancer patients trained at MMC, the patients after SCT had a very low  $VO_{2\max}$  at the start of the program (range 31-115% of the Jones norm, median 60%; the average in healthy persons being 130%), and required more individualized training.

The high intensity strength and interval training program developed at MMC is promising with respect to rehabilitation of cancer patients, but needs to be further explored and tested in the group of SCT patients. This will be done in this multicenter, randomized controlled trial (RCT).

#### 5.2.2 Focus group interviews.

We performed focus group interviews with patients having undergone autologous SCT for MM, HL or NHL in the AMC. Out of 13 patients interviewed, 12 were interested in participating in an exercise-based rehabilitation trial, provided that they would be able to train close to their home. All 12 patients preferred out-of-home supervised training. After explanation of the assessment procedures used in the proposed RCT, all 12 patients had no objections to undergo such testing.

### **5.3 Economic evaluation**

Several studies have shown that patients who have been treated with high dose chemotherapy and SCT use a lot of resources [25-27], and are often not able to return to work [28-31]. To our knowledge, there are currently no data on the cost-effectiveness of exercise intervention programs in these patients. It is therefore important to study whether the high-intensity exercise intervention, is cost-effective in comparison with standard care

### **5.4 Conclusion**

The question which will be answered in the currently proposed study is whether high intensity strength and interval training based on the program by de Backer et al. [23,24] is effective in patients who have undergone high dose chemotherapy and autologous SCT. More specifically, the effects on cardiopulmonary function, muscular strength and fatigue will be evaluated. Furthermore, the cost-effectiveness of the program will be determined.

### **5.5 Hypothesis**

We hypothesize that following the exercise program and standard care will lead to

1. improved physical fitness;
2. lower levels of fatigue;
3. less mood disturbance, higher levels of daily activities, and improved HRQL;
4. a higher partial and full return to work rate when compared to standard care only;
5. will be cost-effective when compared to standard care.

## 6. Study Objectives

Primary objective:

- To evaluate the effectiveness of a state-of-the-art individualized high-intensity exercise program in comparison to standard care with respect to fatigue, physical fitness, and HRQoL in patients with hematologic malignancies who have undergone HDT and autologous SCT.

Secondary objective:

- To evaluate the cost-effectiveness of this exercise program in comparison to standard care.

## 7. Study design

### 7.1 Pilot study

The intervention in this study is based on the program that has been developed and tested at MMC [32,33]. Prior to the trial a pilot study in 5 SCT patients will be performed to evaluate the feasibility, and if necessary fine tuning of the intervention and to test the study logistics. At the end of the program the patient will be interviewed about: (1) the perceived efficacy of and satisfaction with the intervention program and (2) need for changes to the program.

### 7.2 Randomized controlled trial

This multicenter, prospective, single blind, RCT will compare an exercise intervention and standard care with standard care only. The 120 patients participating in the study will be randomized to either the intervention arm (n = 60) or the control arm (n = 60). In addition to the standard care, patients in the intervention arm will take part in an 18-week individualized supervised high-intensity exercise program. This program will start 6-14 weeks after SCT. Patients in the control group are treated according to standard care.

### 7.3 Inclusion and exclusion criteria

#### Inclusion criteria

- Patients diagnosed with MM in first line or with HL/NHL in first line or first relapse, who have undergone HDC and autologous SCT 6 to 12 weeks ago or who were recently (< 8 months) treated with HDC and autologous SCT and who have completed radiotherapy or their last cycle of consolidation chemotherapy 2 to 6 weeks ago..
- Sufficiently recovered from the SCT and having peripheral blood recovery;
- Age  $\geq$  18 years
- Ability to cycle on a bicycle ergometer against a load of at least 25 Watt;
- Ability to walk at least 100 meters independently without crutches/canes or walking frame;
- Written informed consent.

#### Exclusion criteria

- Tandem autologous-allogeneic SCT;
- Severe cognitive impairment;
- Severe emotional instability;
- Insufficient mastery of the Dutch language;
- Presence of extensive osteolytic lesions with risk of fracture;
- Serious cardiopulmonary and cardiovascular conditions;
- Other disabling comorbidity interfering with the intervention program or influencing outcome parameters (a.o. having a pacemaker, epileptic seizures and poorly regulated diabetes mellitus);
- Severe infections;
- Relapse/progression of disease.

### 7.4 Recruitment

Patients will be recruited at the Academic Medical Center (Amsterdam), Antoni van Leeuwenhoek hospital (Amsterdam), St. Antonius Hospital (Nieuwegein), Haga Ziekenhuis (Den Haag), Onze Lieve Vrouwe Gasthuis (Amsterdam), Erasmus MC (Rotterdam), University Medical Center (Utrecht), Isala klinieken (Zwolle), VU University Medical Center (Amsterdam) and Leiden University Medical Center. All potentially eligible patients will be identified and informed of the study by their treating physician. The patients will receive written information of the study to take home.

**7.5 Randomization & blinding**

Randomization will be stratified according to transplant center and diagnosis. Eligible patients will be randomized to one of the two arms: (1) exercise intervention and standard care or (2) standard care. Randomisation will be done using the software package ALEA developed by TENALEA [32].

Outcomes will be assessed by blinded and independent trained professionals. At the beginning of the assessment patients will be instructed not to reveal their group allocation.

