#### 8.4 Timing and location of the investigations

Figure 1 shows the timing of the assessments. The initial screening before start of the intervention ( $t=0$ ) is crucial to identify unknown health problems, to guide exercise, analyse the physiological and muscular limitations that need to be improved by training and to determine the physical loading capacity of individual patients in concert with possible physical limitations [23].

Assessment procedures will be performed at the Academic Medical Center Amsterdam or in Rotterdam (patients Erasmus MC only) according to a detailed and standardized protocol. A physician and the researcher perform the measurements (except for the DXA scan). The assessment of cardiopulmonary fitness and muscle strength will take approximately one hour; filling out the questionnaires at  $t=0$ ,  $t=1$  and  $t=2$  will take 45 minutes (which can be done at home); filling out the cost diaries will take approximately 10-15 minutes each time.

[figure not shown]

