#### 8.5 Required assessments at baseline, after treatment and during follow up

Table 2 shows when the different parameters will be assessed and below the table the associated variables or instruments are listed. The measurements are described in the following paragraph.

Table 2. Measurements at different time points

|                                                        | T0      | T1 | T2             |
|--------------------------------------------------------|---------|----|----------------|
| Clinical data                                   |         |    |                |
| Medical history                            | X       |    |                |
| Disease status and treatment               | X       | X  | X              |
| Adverse events                                         | X       | X  | X              |
| Physical tests                                  |         |    |                |
| Physical examination                       | X       | X  | X              |
| Lab tests                                  |         |    |                |
| Cardiopulmonary fitness                    | X       | X  | X              |
| Muscular strength                          | X       | X  | X              |
| Body composition and bone mineral density  | X       |    | X              |
| Questionnaires                                  |         |    |                |
| Fatigue                                    | X       | X  | X              |
| Health-related quality of life             | X       | X  | X              |
| Physical activity                         | X       | X  | X              |
| Mood disturbance                          | X       | X  | X              |
| Functioning in daily life                 | X       | X  | X              |
| Return to work                            | X       | X  | X              |
| Satisfaction with the intervention        |         | X  |                |
| cost questionnaires                       | Monthly |    | Every 3 months |

1. Date of diagnosis, subtype of disease, stage of disease, history of therapy.
2. Response to treatment, progression or relapse of disease and data on any additional treatment will be recorded from medical records.

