#### 2. Muscular strength

Muscular strength refers to the external force that can be generated by a specific muscle or muscle group. Upper extremity muscular strength will be assessed using a grip strength dynamometer and lower extremity muscular strength by the '30 s chair stands' test. In addition muscular strength of the m. quadriceps will be measured isometrically using a fixed dynamometer (Biodex System).

Maximal handgrip strength is performed three times for each hand. The mean score attained for each side will be recorded. The '30 s chair stand' test has been demonstrated to be a valid and reliable measure of proximal lower limb strength in older adults. The subject is asked to stand upright from a chair with arms folded across the chest, then to sit down again and then repeat the action at his/her own/fastest pace over a 30 s period. The final test score is the number of times that the subject rises to a full stand from the seated position with arms folded within 30 s [39]. To assess the strength of the m. quadriceps, patients will also be asked to perform three maximal voluntary knee extensions with the dominant leg at 60 degrees knee angle. The highest peak torque (Nm) of the three attempts will be used for analysis.

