#### 4. Costs from a societal perspective

Costs will be measured from a societal perspective. The following are considered in this study:

- Health care costs: the costs of oncological care, general practice care and physiotherapy; additional visits to other health care providers, prescriptions of medication, professional home care and hospitalization.
- Patient and family costs: out-of-pocket expenses (e.g. travel expenses), costs for sports and sports equipment, and costs of paid and unpaid help.

- Costs due to loss of production (absenteeism for patients with paid jobs and hours of inactivity for patients without a paid job).

These data will be collected through retrospective cost questionnaires administered on a monthly basis during the period between T=0 and T=1, and once every 3 months in the period between T=1 and T=2. Health care utilization will be valued using Dutch cost prices [52].

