### 9.4 Monitoring of compliance and attrition

Compliance with the exercise program in the intervention arm will be assessed by self-report and by objective measures (e.g., attendance at and duration of the exercise sessions, exercise logs, target intensity). Reasons for noncompliance/nonattendance will be recorded.

Subjects can withdraw from the study at any time for any reason if they wish to do so without any consequences. When applicable, patients will be approached to ask for their reasons. The investigator can decide to withdraw a subject from the study for urgent medical reasons. Individual subjects will not be replaced after withdrawal. The principle of intention-to-treat will be applied in this study. Subjects who have withdrawn from treatment will be asked to participate in the follow-up measurements.

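### Adverse events are scheduled only at the blinded test visits, and no between-visit AE collection offsets the exercise arm's extra supervised contact

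*Protocol*

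**What the plan says.** Section 7.5 claims single blinding through the assessors: "Outcomes will be assessed by blinded and independent trained professionals". The stated safeguard is an instruction to the patient: "At the beginning of the assessment patients will be instructed not to reveal their group allocation".

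Section 8.4 says who does the work at these visits: "A physician and the researcher perform the measurements (except for the DXA scan"). Nobody else is named as taking the AE history.

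Table 2 in section 8.5 has a row "Adverse events" marked at T0, T1 and T2, the same three columns as cardiopulmonary fitness and muscular strength. The section announces that "Table 2 shows when the different parameters will be assessed and below the table the associated variables or instruments are listed", but the AE row carries no note. Section 9.3, item 5, adds only the grading system.

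Between T0 and T1 the exercise arm attends supervised training. Section 9.4 provides for logs in that arm and adds: "Reasons for noncompliance/nonattendance will be recorded". Both arms complete "retrospective cost questionnaires administered on a monthly basis during the period between T=0 and T=1", then one every 3 months to T2. These cover hospitalization, physiotherapy, visits to other care providers and medication. Section 10 makes no use of them.

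**The concern.** Two of the three primary outcomes depend on maximal effort, and a tester's encouragement can influence effort. In the strength assessment, for example, patients "perform three maximal voluntary knee extensions with the dominant leg at 60 degrees knee angle". If the same people ask at T1 about the past 18 weeks, a patient injured in training has two duties that pull against each other: to give a full account and to keep the allocation hidden. The protocol does not say how this is managed.

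The second issue is detection. An event in the exercise arm can come to a therapist's notice in the week it happens. In a control, a non-serious event between T0 and T1 has no scheduled AE enquiry until T1. At stake are the single-blind claim for some patients and the fairness of any safety summary by arm. For a high-intensity programme, safety is one of the first things a reader will look for.

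**Working it through.** **1. Visits and tests (Table 2, sections 8.4, 9.1).** AEs, the VO2max test, handgrip, chair stands and quadriceps dynamometry all fall at T0, T1 and T2. T1 and T2 matter here, because by then the patient has an allocation to disclose. No order of AE enquiry and testing is fixed, and no separate AE collector is named. Fatigue, the third primary outcome, is a questionnaire that can be filled in at home, so tester blinding matters less for it.

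**2. Scheduled contact between T0 and T1.** Table 1 gives two sessions a week in weeks 1-12 and one a week in weeks 13-18:

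2 × 12 + 1 × 6 = 30 sessions.

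This reproduces the protocol's total. Six counselling contacts come on top, one of them at week 22, after training ends. Controls have no scheduled supervised contact. The 30 sessions are opportunities to notice an event, not 30 AE enquiries, because nothing gives the therapist a duty to record AEs.

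**3. The source common to both arms.** Monthly questionnaires over an 18-week programme:

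18 ÷ (52/12) = 4.15, so about 4 per patient before T1, equally in each arm.

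**4. What happens to an undetected event.** Section 10.2 makes hospitalization an SAE. Section 10.3 relies on event-driven reports and takes a patient with no SAE report to be alive and free of SAEs. Non-detection is thus recorded as no event. Section 7.4 lists ten recruiting hospitals, while section 8.4 places assessments in Amsterdam or Rotterdam. A control's admission elsewhere reaches the study through an event-driven report, record retrieval or monitoring, or through the cost questionnaire, which is not linked to safety reporting.

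**5. Illustration of unequal detection.** The protocol gives no detection rates, so every rate here is an assumption. Let the true AE risk be equal in both arms, with 90% of events detected in the exercise arm, proportion c detected in controls, and 60 patients per arm. The apparent risk ratio is 0.90/c. The chance of a nominally significant false difference is approximately Φ[(|p₁ − p₂| − 1.96 × SE₀)/SE₁], where p₁ = 0.90 × risk, p₂ = c × risk, SE₀ is the pooled and SE₁ the unpooled standard error.

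| True risk | c | Expected recorded, exercise vs control | Apparent ratio | Chance of false difference |
|---|---|---|---|---|
| 20% | 70% | 10.8 vs 8.4 | 1.29 | 9% |
| 40% | 70% | 21.6 vs 16.8 | 1.29 | 15% |
| 20% | 50% | 10.8 vs 6.0 | 1.8 | 24% |
| 40% | 50% | 21.6 vs 12.0 | 1.8 | 50% |

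With c also at 90% the ratio is 1.0. The table shows how the result moves with the assumption. It does not estimate what will happen in this trial.

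**6. A related window.** Section 10.1 defines AEs as occurring during protocol treatment, which section 10 ends 30 days after the end of treatment (or earlier, at another systemic anti-cancer treatment). Table 2 nevertheless marks AEs at T2. The two should be reconciled, because this settles what any AE items after T1 are for.

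**The case against.** A reader might infer that every training injury must either unblind the tester before the tests or go unrecorded. The documents do not support that. The instruction covers allocation, not symptoms, so a knee strain can be reported without its cause. No order is stated, and AE questions may follow the tests. In Table 2 the AE row stands under clinical data, beside disease status, which is taken from medical records, so the mark at T1 need not mean an interview by the tester. The detailed assessment protocol mentioned in section 8.4 may settle order and roles. Injury also has other routes: a reason for going off protocol treatment (8.3), a reason for a missed session (9.4), and SAE reporting (10.3).

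A reader might also infer that only the exercise arm is observed between visits. That is not so. SAE reporting, record retrieval (9.3), cost questionnaires and source-data monitoring (13.1) apply to both arms, and scheduled AE collection is identical. Section 11 plans no between-arm AE test. The background reports good tolerance of the programme, and no adverse effects in eight transplanted patients, so few patients may be affected.

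All of this stands, and it limits the point to a risk. It does not remove it. The routes common to both arms are event-driven or retrospective and do not assure capture of non-serious events, and the routes through training exist in one arm only. Patient discretion remains the only safeguard stated for a blinded tester. Even a purely descriptive AE table by arm would carry any difference in detection.

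**Conclusion.** The point holds as a weakness in data collection. AE enquiry shares its visits with blinded, effort-dependent tests and is not separated from them, so a training injury may disclose the arm or be described incompletely. Between visits, only the exercise arm has scheduled supervised contact, 30 sessions against none, so non-serious events and hospitalizations may be detected more readily there. Neither the number of patients unblinded nor the difference in detection can be derived from the protocol; the ratios of 1.29 and 1.8 rest wholly on assumed detection rates.

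The conclusion assumes that at least part of the AE history is taken from the patient at T1 and T2, as Table 2 suggests but does not say. If AEs are drawn only from records, the blinding part falls away and the detection part remains. The matter is worth settling before recruitment, because events never asked about cannot be recovered in the analysis.

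**What to change.** - Add a few allocation-neutral AE items to the existing cost questionnaire, monthly to T1 and 3-monthly to T2, in both arms. Return them to the data manager, not to the person who runs the tests.
- Check every hospitalization reported there against the SAE reports in both arms, allowing for the admissions that section 10.3 exempts.
- Base any AE summary by arm on this equal-schedule source. Report events known only from training logs or missed-session reasons separately.
- At T1 and T2, take any remaining AE history after the primary tests, apart from questions needed to perform the tests safely. State in section 8.4 or 8.5 who takes it.
- Reconcile the AE period in section 10 with the T2 mark in Table 2.

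The cost is a few questionnaire items, one data cross-check and a slight added burden on patients and the data manager. No extra visit or staff is needed. The new items are still retrospective self-report, but recall shortens from about 18 weeks to about one month before T1 and is the same in both arms.
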